**Figure 2 F2:**
[figure not shown]
Summary of the intervention components. AHP, allied health professional; GP, general practitioner.

Participants will also receive usual care and a Stroke Association TIA information sheet. Follow-up for TIA and minor stroke is not standardised; therefore, usual care varies between hospitals, GP practices and individual clinicians. Typically, any secondary care follow-up is related to imaging and investigations to determine cause of the TIA/ minor stroke and inform stroke risk prediction; for example, carotid imaging or ECG. Follow-up in primary care usually focuses on secondary prevention, such as medication and lifestyle advice; however, presence and quality of primary care follow-up post-TIA/minor stroke is variable.

Details of the intervention are described below in accordance with the template for intervention description and replication checklist.^24^ The logic model is depicted in figure 3.

**Figure 3 F3:**
[figure not shown]
Logic model.

#### Materials and procedures

Participants randomised to receive the intervention will be invited to a nurse/AHP-led follow-up appointment. Prior to their appointment, participants will be asked to complete a needs checklist, which will be posted to them prior to the appointment. The checklist comprises 12 potential needs which encompass information provision (diagnosis and stroke risk); secondary stroke prevention (medication and lifestyle change); and holistic care (psychological and psychosocial) (online supplemental appendix 2). The checklist is an adapted version of the Stroke Review Checklist^25^ and was informed by the literature and earlier qualitative research,^7^ codesigned with consumers.

10.1136/bmjopen-2021-060280.supp2Supplementary data

The nurse/AHP will use the checklist to guide discussions to identify participants’ unmet needs. If multiple needs are identified, priority will be given to addressing needs which the participant considers the most significant.

The nurse/AHP will address needs that can be resolved during the appointment, such as information about driving. For needs that cannot be immediately addressed, the nurse/AHP will, where appropriate, refer or signpost to support services and develop an action plan which will be agreed with the participant. Where possible, the nurse/AHP will make referrals; however, in some circumstances GP referral may be required, in which case this will be requested in the GP letter. To facilitate this, the intervention provider will be provided with a website of resources and support services and a list of local services.

The nurse/AHP will take the participants’ blood pressure and, if raised (≥140/90 mm Hg), request for the participant’s GP to review blood pressure in the action plan and GP letter.

If necessary, the nurse/AHP may invite the participant to attend another follow-up appointment, at a suitable time point, to monitor the participant’s progress and revise the action plan if required. These additional follow-ups may be conducted by telephone, video call or face to face.

A letter will be sent to the participant’s GP along with a copy of the agreed action plan. A letter template will include recommended GP actions, a summary of the appointment and actions taken.

The participant will be provided with a self-management booklet (an abridged version of the resources and services website) and a copy of the action plan and GP letter.

#### Intervention provider

The intervention will be delivered by a nurse or AHP, with stroke expertise, who are clinical staff at the participating hospital sites. It is anticipated that 1–2 intervention providers will be trained per site; however, this will depend on availability of clinical staff at sties. The nurses and AHPs will attend training which will include education about potential needs after TIA and minor stroke, and how to deliver the intervention. One training session, approximately 2.5 hours) will be provided remotely (via Zoom); however, ad hoc support and feedback will be encouraged after the training.

#### Setting and modes of delivery

The intervention appointments will be delivered at the site’s TIA clinic, either face to face or remotely (eg, telephone or video call). Face-to-face delivery will be preferable where possible.

#### When and how often

The intervention appointment will take place at 4 weeks (or up to 6 weeks). The appointment is expected to last approximately 30 min. One appointment will be offered initially; however, participants will have an option to attend additional follow-up if judged clinically necessary by the nurse or AHP. There are no predetermined criteria for further follow-up and the criteria used by nurses/AHPs will be recorded as part of the feasibility study to inform future refinement of the intervention.

### Control arm

The control group will receive usual care and be given a Stroke Association TIA information sheet when they are informed about their allocation to the control arm.

### Recruitment

A member of the clinical team will screen patients’ medical records and approach potentially eligible patients face to face or by phone. After confirming eligibility, potential participants will be invited to take part in the study. Informed consent may be taken face to face (for people approached in clinic), by post (for people who need more time to consider participation) or verbally (for people approached via phone). Verbal consent will be clearly documented in the participant’s medical records and the participant will also be sent a postal consent form to compete. Sites will receive a per-participant reimbursement for recruitment.

### Sample size

The study will aim to recruit 60 participants (30 in the intervention group, 30 in the control group). As this is a feasibility study, no formal sample size calculation has been performed; however, the sample size is the estimated number that would be feasible to show that we can recruit these types of patients for this type of study.^26^

### Randomisation

Participants will be randomised 1:1 to either the intervention or control group. A minimisation algorithm will be used within an online randomisation system to ensure balance in the treatment allocation using the following variables: age at consent (<60 years, ≥60 years); sex (male, female); diagnosis (TIA, minor stroke); employment (employed, non-employed/retired).

A ‘random element’ will be included in the minimisation algorithm, so that each patient has a probability, of being randomised to the opposite treatment that they would have otherwise received.

Participants will be randomised at baseline by clinical staff; however, to prevent baseline patient reported outcomes being affected by study arm allocation, participants will be notified of their randomisation allocation after they have returned the 1-week questionnaire or at 3 weeks (if the 1-week questionnaire is not returned). Participants will be notified of their allocation by a letter in the post, which will be sent by the research team at the Trials Unit. Due to the nature of the intervention, it is not possible to blind participants or clinicians delivering the intervention.

### Outcomes and data collection

Table 1 summarises the patient reported, health economic and clinical outcome measures. Contact details, demographic information and medical history will be collected at baseline from medical records or participant interview, by a member of clinical staff. Questionnaires comprising Patient-Reported Outcome Measures (PROMs) (table 2) will be completed by participants, either by post or electronically, at 1, 12 and 24 weeks. PROM rationale for assessment and psychometric properties are presented in online supplemental appendix, eTable 2. Questionnaires at 12 and 24 weeks will also collect health economics data. The first PROM completion will be at 1 week rather than baseline due to the nature of the PROM questions and to reduce burden on participants. Clinical data (table 2) will be collected at an end of study clinic appointment at 26 weeks by a research nurse or clinical staff. Where possible, this appointment will be face to face in the TIA clinic; however, may be delivered remotely if face to face is not an option.

10.1136/bmjopen-2021-060280.supp3Supplementary data

**Table 1 T1:** Summary of patient reported, health economic and clinical outcome measures

	Data	Timepoint
Baseline data	Contact details	Baseline
	Demographic: date of birth, sex, ethnicity, employment status	
	Medical: diagnosis, date of TIA or minor stroke, modified Rankin scale score, length of stay, smoking status, alcohol consumption, height, weight, body mass index, comorbidities, medication, blood pressure, cholesterol	
Patient-reported outcome measure	Health related quality of life: Patient-Reported Outcomes Measurement Information System-Global Health 10	1, 12 and 24 weeks
	Health related quality of life: 5-level EuroQol 5-Dimensions	
	Anxiety/depression: Hospital Anxiety and Depression Scale	
	Fatigue: Fatigue Assessment Scale	
	Self-efficacy: Patient Activation Measure-13	
	Medication adherence: Medication Adherence Rating Scale−5	
	Satisfaction with overall care after TIA/minor stroke question: 5-point Likert scale (very satisfied – very dissatisfied)	
Health economics	Use of healthcare services	12 and 24 weeks
	Change in employment status, altered work hours and days off sick	
	Other costs incurred because of TIA or minor stroke	
Clinical data	Body mass index	Baseline and 26 weeks
	Blood pressure	
	Bloods: cholesterol	
	Medications	

TIA, transient ischaemic attack.

**Table 2 T2:** Feasibility outcomes and measurement of outcomes

Objective	Feasibility outcomes	Measurement of outcome
(A) Assess feasibility and acceptability of the trial design and methods	No of eligible/ineligible patients and reasons for ineligibility	Recruitment log
	Proportion of participants who consent face to face, verbal or postal	Registration log: method of consent
	Willingness of clinical staff to randomise patients	Interviews (clinical staff involved in randomisation)
	Recruitment and attrition rates	Registration log
	Response rates and frequencies of missing data: participant completed questionnaires and case report forms	1, 12 and 24 weeks questionnaires Case report forms
	End of study clinic appointment attendance rates	End of Study Clinic Appointment Form
	Acceptability of the trial design	Interviews (participants and clinical staff) Structured observations
(B) Provide data to inform the sample size for a definitive randomised controlled trial	SD of continuous patient reported outcome measures at 6 months	Patient reported outcome measure scores
	Recruitment and attrition rates	Registration log
(C) Provide data to help inform selection of the primary outcome measure for a definitive randomised controlled trial	Correlation of patient reported outcome measures	Patient reported outcome measure scores
	Patient reported outcome measure response rates and missing data	1, 12 and 24 weeks questionnaires

#### Feasibility outcomes and process evaluation

The feasibility study and process evaluation outcomes are detailed in tables 2 and 3. The process evaluation is underpinned by the National Institutes of Health’s Behavioural Change Consortium treatment fidelity framework.^27^ This framework includes five domains of treatment fidelity: Study Design, Training, Delivery, Receipt and Enactment.

**Table 3 T3:** Process evaluations outcomes and measurement of outcomes

NIH BCC domain	Objective	Outcome	Measurement of outcome
Study design	d) Investigate acceptability of the intervention for participants and intervention providers	Participants’ and intervention providers’ opinion on acceptability of the intervention	Interviews (participants and intervention providers) Feedback questionnaire (intervention participants)
	e) Test hypotheses relating to the theoretical underpinning of the intervention	Participants’ satisfaction with identification and management of needs	Interviews (participants and intervention providers) Feedback questionnaire (intervention participants)
		Participants acting on agreed action plans and/or accessing support services	Interviews (participants)
Training	f) Assess if intervention providers are adequately trained to deliver the intervention	Intervention providers’ understanding of the intervention components	Interviews (intervention providers)
Delivery	g) Assess adherence to the intervention	Intervention providers’ adherence to and deviations from the intervention manual	Structured observations Intervention log
	h) Assess contamination with the control group	Control group contamination	Interviews (participants and clinical staff) Structured observations
	i) Define the ‘dose’ of the intervention	Intervention follow-up appointment: attendance, length of appointment and number of appointments	Intervention log
Receipt	j) Explore how well intervention participants received and understood the intervention	Participants’ perception of the intervention	Interviews (participants) Feedback questionnaire (intervention participants)
Enactment	k) Explore to what extent the intervention was enacted as intended by intervention participants	Participants acting on agreed action plans and/or accessing support services	Interviews (intervention participants)

BCC, Behavioural Change Consortium; NIH, National Institutes of Health.

##### Case report forms

The following case report forms will collect data on feasibility outcomes: recruitment log (recruitment rates and reasons for ineligibility); registration log (method of consent: face to face/verbal/ postal); intervention log (attendance rates, duration, number of appointments per participant); end of study clinic appointment form (attendance). Case report forms will be assessed for missing data. The following intervention documents will capture information on needs, what was discussed and action plans: checklist, action plan and GP letter.

##### Participant completed questionnaires

Participant completed questionnaires (1, 12 and 24 weeks) will be analysed for response rates and missing data. SDs of continuous PROMs at 6 months and correlation of PROMs will inform the sample size and selection of outcome measures for the definitive RCT. The intervention feedback questionnaire will report acceptability of the intervention. A paper copy of the feedback questionnaire and prepaid envelope will be posted to participants after the intervention appointment. This questionnaire contains 5-point Likert scale questions (eg, strongly agree—strongly disagree) and free text questions about experiences of the checklist, appointment and action plan.

##### Structured observations

A member of the study team will observe the following study processes: recruitment and consent procedures; intervention appointments; and end of study clinic appointments. Both face to face and remote modes of delivery will be observed for these procedures if possible. A target of three observations will be conducted for recruitment/consent and end of study clinic appointments (one at each site). A target of two intervention appointments will be observed per site (20%). More observations may be conducted if deemed necessary; for example, multiple clinical staff performing each procedure. A pragmatic approach will be taken to select which sessions to observe based on the availability of the research and clinical teams. A checklist will be used to document adherence to the protocol and field notes will be collected.

##### Audit

At the end of the recruitment period, each site will perform an audit to identify the total number of confirmed TIA and minor stroke patients who attended the TIA clinic or stroke ward during the recruitment period. The age and sex of these patients will also be collected. This data will be used to compare average age and sex of patients recruited to the trial against patients not recruited.

##### Qualitative interviews

At the end of the study, semistructured interviews will be conducted with a subset of participants and clinical staff involved in recruitment and/or intervention delivery. The sample size is anticipated to be 8–10 patients and 4–6 clinical staff (including those involved in recruitment/consent, intervention delivery and end of study clinic appointments). For patient participants, convenience sampling will be used initially; however, sampling will become increasingly purposeful to achieve variation in age (<60 years, ≥60 years) and diagnosis (TIA, minor stroke). For clinical staff, convenience sampling will be used. Interviews will be conducted by GT, an experienced qualitative researcher. Interviews will be face to face (home/ hospital), telephone or video call, depending on the participants preference. Interviews will explore acceptability of the intervention and trial design. Semistructured topic guides will include discussion of the following:

Patient participants:Intervention: intervention and trial design acceptability; how well intervention participants received and understood the intervention; extent to which intervention providers addressed needs; if the action plan was actioned; facilitators and barriers to enactment.Control: trial design acceptability; intervention contamination.Both: what care/support participants received; understanding what comprised usual care.Staff participants: acceptability of the trial design; experience of training day and understanding of the intervention; acceptability of delivering the intervention; facilitators and barriers to implementing both the trial design and the intervention; and experience of contamination with the control group.

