## Introduction

Transient ischaemic attack (TIA) and minor stroke are important risk factors for stroke. Over 46 000 people experience a first TIA or minor stroke per year in the UK,^1^ 240 000 in the USA^2^ and 0.31 million in China.^3^

National guidelines promote long-term management that focuses on stroke prevention.^4–6^ However, research shows TIA and minor stroke patients feel unsupported in stroke prevention—both medication and lifestyle change—and often lack basic understanding of their diagnosis, stroke risk and preventative medication.^7^ Furthermore, many people experience a wide variety of residual impairments and unmet needs after TIA or minor stroke, including anxiety, mood/ emotional impact, fatigue, cognitive impairment, physical weakness, visual impairment and impaired speech.^8–17^ TIA and minor stroke have been also reported to impact on people’s ability to return to work, performance at work, social activities and family relationships.^12–19^ Follow-up care is variable and often inadequate with patients feeling abandoned after hospital discharge.^7^

Care needs after TIA and minor stroke include information provision (diagnosis and stroke risk); stroke prevention (medication and lifestyle change) and holistic care (residual problems and return to work or usual activities).^7^ However, there is no evidence for how to best support these patients after rapid specialist review in hospital. To address this, we developed a multifaceted intervention which aims to actively identify and address unmet needs after TIA and minor stroke: Structured follow-Up Pathway to imProve management Of Residual impairmenTs and patients’ quality of life after TIA and minor stroke. The components of the intervention are described in this protocol. In accordance with the Medical Research Council guidance on developing and evaluating complex interventions,^20^ we will evaluate the feasibility and acceptability of (1) the intervention and (2) the trial procedures for a future randomised controlled trial (RCT) of this intervention. In addition, we will conduct a process evaluation to evaluate intervention fidelity and contextual influences on delivery.

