### Study setting and eligibility criteria

Participants will be recruited from TIA clinics and stroke wards at three tertiary hospital sites in England, one in South East England (Berkshire) and two in North West England (Wigan and Liverpool). Participants will be adults who have experienced a first or recurrent TIA or minor stroke. The full eligibility criteria are detailed in box 1.

Box 1Eligibility criteriaInclusion criteriaAdults (aged ≥18 years).Resident in England.Diagnosis of confirmed transient ischaemic attack (TIA) or minor stroke by a stroke consultant. TIA will be defined as a transient episode of neurological dysfunction caused by focal brain, spinal cord or retinal ischaemia, without acute infarction.^30^ Minor stroke will be defined as a modified Rankin scale score ≤1 or no change in modified Rankin scale score from pre-event (to account for people who were disabled prior to their TIA or minor stroke)*.Attending the TIA clinic or stroke ward for a new diagnosis of TIA or minor stroke, rather than for a follow-up appointment.Ability to converse in everyday English and read in English.Capacity to provide fully informed consent for participation in the trial.Exclusion criteriaHistory of full stroke (modified Rankin scale score >1).History of dementia.People who lack capacity to participate, such as if they have severe memory problems that mean they would not remember giving consent or if they have severe communication problems, not precluding patients who use electronic devices to communicate.Patients receiving early supported discharge or cardiac rehabilitation.Patients receiving any palliative care.

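### Site is not a sampling factor for the interviews, although two process-evaluation outcomes are measured by interview alone and implementation across sites is a stated strength

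*Protocol article*

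**What the plan says.** The strengths list at the front of the protocol article says that the multicentre design allows implementation to be explored in different site contexts. The Introduction adds that "we will conduct a process evaluation to evaluate intervention fidelity and contextual influences on delivery". Recruitment is at "three tertiary hospital sites in England", and the Intervention section notes that usual care differs between hospitals. Each site has its own staff delivering the intervention: "It is anticipated that 1–2 intervention providers will be trained per site".

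The Qualitative interviews section sets the numbers: "The sample size is anticipated to be 8–10 patients and 4–6 clinical staff". Patients are first taken by convenience, after which "sampling will become increasingly purposeful to achieve variation in age (<60 years, ≥60 years) and diagnosis (TIA, minor stroke"). For staff the rule is shorter: "For clinical staff, convenience sampling will be used". Neither rule mentions site, and no split of patient interviewees by arm is given.

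Table 3 gives interviews with intervention providers as the only measure for objective f (understanding of the intervention components). It gives interviews with intervention participants as the only measure for objective k (acting on action plans or accessing support). The other Table 3 objectives have a further source, except that the action-plan outcome under objective e also rests on interviews alone.

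Other elements are tied to site. For the observations of trial procedures, "A target of three observations will be conducted for recruitment/consent and end of study clinic appointments (one at each site"). Two intervention appointments are to be observed per site, and each site performs an audit at the end of recruitment.

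**The concern.** With three sites, separate providers and usual care that varies by hospital, site is the most obvious context variable. The sampling rules secure variation in age and diagnosis but leave coverage of sites to chance and availability.

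This matters most where the interview is the only instrument. If no provider at a site is interviewed, nothing planned shows whether training was understood there. If no intervention participant from a site is interviewed, nothing planned shows whether action plans were acted on there. The study could then describe training and enactment for two sites and be silent on the third, while claiming site comparison as a strength.

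**Working it through.** **Inputs from the protocol article.** Three sites (Study setting and eligibility criteria). Sample size: "The study will aim to recruit 60 participants (30 in the intervention group, 30 in the control group"). Interviews: 8–10 patients and 4–6 staff (Qualitative interviews). Providers: 1–2 per site, so 3–6 in all (Intervention provider).

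**The plan's own figure.** Two observed intervention appointments at each of three sites, against 30 intervention participants with one first appointment each, is 2 × 3 / 30 = 6/30 = 20%, as stated under Structured observations. This is consistent with 10 intervention participants per site but does not establish it. Site is not among the minimisation variables, so intervention numbers per site are not balanced by design.

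**Assumptions, not in the protocol.** Site sizes, the arm split of interviewees and a random draw. Convenience sampling may cover sites better or worse than a random draw, so the figures illustrate scale and do not predict the outcome.

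**Formula.** For three equal sites of size m, with n interviewees drawn at random from 3m people, the chance that at least one site has none is

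[3·C(2m, n) − 3·C(m, n)] / C(3m, n).

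**Intervention-arm interviewees, m = 10:**
- n = 4: 3 × (4,845 − 210) / 27,405 = 13,905 / 27,405 = 50.7%
- n = 5: 3 × (15,504 − 252) / 142,506 = 45,756 / 142,506 = 32.1%
- n = 6: 3 × (38,760 − 210) / 593,775 = 115,650 / 593,775 = 19.5%

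**Any patient interviewee, either arm:**

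| Site sizes | 8 interviews | 10 interviews |
|---|---|---|
| 20/20/20 | 9.0% | 3.4% |
| 30/20/10 | 24.0% | 14.7% |
| 40/10/10 | 39.0% | 26.1% |

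**Any staff interviewee, assuming three eligible staff per site:**
- n = 4: 3·C(6,4)/C(9,4) = 45/126 = 35.7%
- n = 5: 3·C(6,5)/C(9,5) = 18/126 = 14.3%
- n = 6: 3·C(6,6)/C(9,6) = 3/84 = 3.6%

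These staff figures count any role. Objective f needs a provider, so the relevant chance is at least as high if some of the eligible staff at a site do not deliver the intervention.

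**With the proposed rule.** One intervention participant and one provider per site uses three patient and three staff interviews. That leaves 8 − 3 = 5 to 10 − 3 = 7 patient interviews and 4 − 3 = 1 to 6 − 3 = 3 staff interviews for other purposes. If the aim is met, no site is missed on f or k.

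**The case against.** The case against is substantial, and much of it stands.

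- **No site goes unstudied.** Observations are set per site, including two intervention appointments at each, with a checklist and field notes. Each site does an audit. The intervention log covers intervention participants generally, and the feedback questionnaire, with free-text questions, is posted after the intervention appointment and is not limited to interviewees. The gap is confined to what is measured by interview alone.
- **Context is not absent.** The interview topic guides cover barriers and facilitators for staff, barriers to enactment for intervention patients, and what usual care comprised. The strengths statement says the design enables exploration; it does not promise a site-stratified analysis.
- **The provider pool is small.** With 3–6 providers and 4–6 staff interviews, all sites may well be reached in practice. But staff interviews must also cover recruitment/consent and end-of-study clinic roles, and nothing in the text secures coverage of sites.
- **The probabilities rest on assumptions**, as stated above, and the 20–51% range concerns intervention-arm interviewees only.

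A reader might also infer that the progression criteria are defective because a failing site can hide behind a green total. The document does not support that as a fault. Two of the six criteria (delivery and acceptability) are overall committee judgements with no numeric band. With 10 intervention participants per site, a green attendance of 27/30 implies at least 27 − 20 = 7 of 10 at any one site, which is 70% and amber. A red site is arithmetically possible for the 24-week return: 8/20 (40%) with 40/40 elsewhere gives 48/60 = 80%. But that needs perfect return at the other two sites. A study-level percentage is a natural measure for a multicentre feasibility question. A by-site table is ordinary analysis-plan or reporting content; the SAP is not shown, and the Analysis section does not preclude such a table.

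**Conclusion.** The point holds for the interview sampling frame only, and it is minor. The protocol article names site context as something the study will explore, fixes interview sampling factors that leave site out, and measures objectives f and k by interview alone. Followed as written, the plan can leave a site without data on either.

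Under random draws and equal sites, the chance of missing at least one site is 51% to 20% for 4 to 6 intervention-arm interviewees, and 9% to 3% for 8 to 10 patient interviewees of either arm. It is higher if sites are unequal. No treatment comparison, error rate or sample size is affected, and the progression criteria are not shown to be wrong.

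**What to change.** In the Qualitative interviews section, add site to age and diagnosis as a purposive factor for patients, and replace pure convenience sampling of staff with sampling that takes account of site and role. Word it as an aim, since people may decline: at least one intervention provider and at least one intervention-arm participant interviewed from each site, within the existing 8–10 patient and 4–6 staff interviews.

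The cost is a change of wording and somewhat less freedom in convenience selection. With only four staff interviews, one would remain for other roles unless providers also recruit or run the end-of-study clinic, so the upper end of the staff range would be more comfortable.

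Optionally, show the Study Oversight Committee the Table 4 percentages by site next to the pooled value. Keep this descriptive and without site-level thresholds: at about 10 per site, one non-attender moves attendance by 10 percentage points.
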